### Type of trial

This is a prospective, randomized, interventional, and patient-blinded, single-center trial comparing two parallel groups.

#### Randomization

To achieve intervention groups with comparable known and unknown risk factors, randomization will be performed. The randomization number will be generated using computer-generated random numbers with an allocation ratio of 1:1 (an equal probability of assignment to either group). All patients will be randomized using consecutively numbered opaque envelopes that will have been sealed by the investigators. The envelopes will be opened before PJ reconstruction and after resection of the lesion from the pancreatic or periampullary region.

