#### Withdrawal

Patients can withdraw from the trial at their own request or at the request of their legal representative at any time. Patients may be removed if, in the investigator’s opinion, continuation of the trail could be detrimental to the patient’s well-being or if a PD is not performed due to technical unresectability, metastatic disease, or other reasons. Every withdrawal will be recorded in the clinical report forms (CRFs) and in the patient’s medical case records. All examinations scheduled for the final trial day will be performed on all patients and documented. All data will be analyzed according to the intention-to-treat (ITT) principle [17].

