#### Ethics, study registration, and consent

The final protocol has been approved by the Ethics Committee of the Second Affiliated Hospital of Anhui Medical University (approval number: KY201502). The trial protocol has also been registered in the protocol registration system at ClinicalTrials.gov (identifier: NCT02511951). All patients will be scheduled only after comprehensive information concerning the nature, scope, and possible consequences of the clinical trial has been provided to them in an understandable way by the investigator. Written informed consent for the study will be obtained from each patient before the operation. The study procedure, benefits, risks, and data management will be clarified in detail during the preoperative conversation.

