#### Blinding

Patients and outcome observers will be blinded with respect to the trial intervention. Blinding of the surgeons and people involved in the operation is not feasible due to the nature of the interventions.

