### Data management and quality assurance

An independent study doctor ([name]), who will not be involved in the treatment and monitoring of the patients within the operating room, will enter all required data in the prepared CRF. This CRF will be completed as soon as possible, preferably on the day of the patient’s treatment and visit (Table 3). Reasonable explanations should be given for all missing data. Complete CRF pages will be checked by the principal investigator and the responsible monitor with respect to completeness and plausibility.

**Table 3 Tab3:** Flow chart of the trial

	Screening					
	Visit 1	Visit 2	Visit 3	Visit 3	Visit 3	Visit 4
	Before surgery	Day of surgery	(POD^b^ 1)	(POD 3)	(POD 7)	(POD 90)
Selection criteria						
Informed consent	×					
Past medical history						
Personal data^a^	×					
Physical examination	×					
Laboratory tests	×		×	×	×	×
Trial intervention		×				
Intraoperative outcomes		×				
Postoperative outcomes			×	×	×	×

^a^Height (cm), weight (kg), gender, immunosuppressant medication, antibiotics, chemotherapy

^b^Postoperative day

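### Envelopes sealed by the investigators, with no independent preparer named, leave allocation concealment unprotected

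*Protocol article*

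**What the plan says.** The Randomization section describes the sequence: "The randomization number will be generated using computer-generated random numbers with an allocation ratio of 1:1". It delivers the allocation by "consecutively numbered opaque envelopes that will have been sealed by the investigators". On timing it says: "The envelopes will be opened before PJ reconstruction and after resection of the lesion". It does not say who generates the list or who keeps it.

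Two other sections give the investigator tasks that affect who enters and stays in the trial:

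- Ethics, study registration, and consent: the information on the trial "has been provided to them in an understandable way by the investigator".
- Withdrawal: "Patients may be removed if, in the investigator’s opinion, continuation of the trail could be detrimental to the patient’s well-being". The same section allows removal when the planned resection is not carried out, and requires every withdrawal to be recorded.

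The Type of trial section states that there is one centre. The Statistical analysis section plans intention-to-treat analysis and adjustment for pancreatic texture (soft or hard) and main duct diameter (below 3 mm, or 3 mm and above).

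**The concern.** Opaque, sealed, numbered envelopes hide the next allocation from people who did not prepare them. They do not hide it from the person who put the allocation inside. The protocol gives the sealing to the role that also speaks with patients before consent and may take them out of the trial. It describes nothing that separates these tasks.

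What is at stake is selective entry. Someone who knows the next allocation could let it affect which patient is approached, in what order patients are scheduled, or whether a patient is removed before the envelope is opened. The Background section justifies the trial by the risk of selection bias in two retrospective comparisons, and the Randomization section says that randomization is there to balance known and unknown risk factors. An open route for selection at entry weakens the property for which the trial is being run.

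**Working it through.** The point rests on who does what, so the check sets the sections side by side.

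1. **Preparation.** The envelopes are sealed by the investigators (Randomization). This is a stated assignment, not a gap in the text.
2. **Entry.** The investigator informs patients before consent (Ethics, study registration, and consent).
3. **Removal.** The investigator may remove a patient on opinion (Withdrawal). Nothing limits this to the time after the envelope is opened.
4. **Separation.** No section states that those who seal are different people from those who recruit or operate. The authors do name independence for another task: the doctor who enters the data is someone "who will not be involved in the treatment and monitoring of the patients within the operating room". No comparable safeguard is given for the envelopes.
5. **Timing.** Opening after resection keeps the allocation from anyone who did not prepare the envelope until the patient is committed. It does nothing against prior knowledge in the person who sealed it.

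Steps 1 to 4 show that foreknowledge is possible under the procedure as written. They do not show that it occurs.

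Would the planned analysis repair the harm if it did occur?

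- **Intention to treat** keeps each randomized patient in the assigned group. A patient who was never approached, or who was removed before an envelope was opened, has no assigned group and is outside its reach.
- **Adjustment for texture and duct diameter** can correct imbalance in those two binary factors. It cannot correct selection on other features, or on differences within a category, such as how far a duct lies below 3 mm.

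Does the point touch the sample size? The inputs from the Patient involvement section are 4.5% and 26.7% fistula, two-sided 5% level, 90% power and 10% withdrawal. With unpooled variance:

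- Sum of variances: 0.045 × 0.955 + 0.267 × 0.733 = 0.0430 + 0.1957 = 0.2387
- Squared difference: 0.222² = 0.04928
- n per group = (1.960 + 1.2816)² × 0.2387 / 0.04928 = 50.9, so 51
- With withdrawal: 102 / 0.9 = 113.3, so 114

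The stated figures reproduce. None of the inputs depends on who seals the envelopes, so the change proposed here leaves them as they are.

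**The case against.** The strongest reply is that the procedure has most of the recognised safeguards. The sequence is computer-generated, and the envelopes are consecutively numbered, opaque, sealed and opened late. The word investigators may be a collective term for a study team that includes people outside the operating room. A journal article may leave the custody of the list to the full protocol. Once the resection is done, reconstruction cannot wait for a different envelope. No exclusion criterion concerns texture or duct diameter, and every withdrawal has to be recorded.

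Much of this stands. Late opening is normally a safeguard and is not part of the fault. Silence on who holds the list would not be a finding by itself. It is also right that selection after inspection of the gland has only a narrow route, namely removal on opinion. What does not fall away is the sentence that assigns the sealing. It is a stated rule, it names the wrong role, and the routes before surgery (approach and scheduling) remain open.

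Three stronger readings are tempting, and the document does not support them.

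- **That concealment is already lost.** The text does not say that those who seal also recruit or operate, or that they see the contents when sealing.
- **That other unblinded roles add to the problem.** A reader might add that "Complete CRF pages will be checked by the principal investigator and the responsible monitor", or that "Blinding of the surgeons and people involved in the operation is not feasible". Both concern knowledge of the treatment after allocation, which is a matter of blinding and not of concealment. The protocol blinds patients and outcome observers.
- **That steering one patient would change the trial's result.** One can pick a borderline table where this happens, but it says nothing about envelopes. At the planning rates, 57 per group gives about 57 × 0.045 = 2.6 and 57 × 0.267 = 15.2 fistulas. With 3/57 against 15/57 the Pearson P value is 0.002, and with 2/56 against 15/57 it is 0.0007, so the conclusion is the same.

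**Conclusion.** The concern holds in a limited form: as written, the procedure leaves allocation concealment unprotected, and foreknowledge is possible but not shown. The conclusion assumes that the word investigators in the Randomization section means the same role as in the consent and withdrawal sections, and that whoever seals an envelope is able to know its contents. The text neither confirms nor excludes either assumption.

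The size of any bias cannot be derived from the document, because it gives no information on how often entry or removal could be influenced. The correction is justified because it is cheap and because the analysis could not undo the bias afterwards.

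**What to change.** For the patients still to be randomized (the Trial status section gives recruitment to December 2018):

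- An existing staff member with no part in recruitment, surgery or outcome assessment generates the sequence, prepares and seals the envelopes, and holds the list.
- Patient ID and date/time are written on each envelope before it is opened.
- Unopened envelopes are replaced with a newly generated set if the people who prepared them recruit or operate. If they do neither, replacement is not needed.
- If an independent person already prepares the envelopes, only the sentence in the Randomization section needs correcting.

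The cost is a few hours of existing staff time and a short amendment.

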#### Blinding

Patients and outcome observers will be blinded with respect to the trial intervention. Blinding of the surgeons and people involved in the operation is not feasible due to the nature of the interventions.

### Data management and quality assurance

An independent study doctor ([name]), who will not be involved in the treatment and monitoring of the patients within the operating room, will enter all required data in the prepared CRF. This CRF will be completed as soon as possible, preferably on the day of the patient’s treatment and visit (Table 3). Reasonable explanations should be given for all missing data. Complete CRF pages will be checked by the principal investigator and the responsible monitor with respect to completeness and plausibility.

**Table 3 Tab3:** Flow chart of the trial

	Screening					
	Visit 1	Visit 2	Visit 3	Visit 3	Visit 3	Visit 4
	Before surgery	Day of surgery	(POD^b^ 1)	(POD 3)	(POD 7)	(POD 90)
Selection criteria						
Informed consent	×					
Past medical history						
Personal data^a^	×					
Physical examination	×					
Laboratory tests	×		×	×	×	×
Trial intervention		×				
Intraoperative outcomes		×				
Postoperative outcomes			×	×	×	×

^a^Height (cm), weight (kg), gender, immunosuppressant medication, antibiotics, chemotherapy

^b^Postoperative day

### Statistical analysis

The two-sided null hypothesis for the primary endpoint measurement states that both study interventions will lead to a similar POPF occurrence rate; the alternative hypothesis is that one intervention will perform better than the other. The null hypothesis will be tested by analyzing the covariance while adjusting for pancreatic texture (soft or hard) and main pancreatic duct diameter (<3 mm or ≥3 mm). A binary logistic regression will be applied to compare the POPF occurrence rates between the groups after adjusting for other factors. Background characteristics and surgical outcome measures will be compared using chi-squared or Fisher’s exact tests for categorical data and two-tailed *t* tests or nonparametric Mann–Whitney *U* tests for continuous variables. Categorical data will be presented as frequencies and group percentages, and continuous variables will be expressed as the means and standard deviations. The homogeneity of two groups will be described by comparison of the demographic data and baseline values. All analyses will be performed on an ITT basis [17]. For the ITT analysis, the data will be processed for all trial patients in their randomized groups. A *P* value < 0.05 will be considered statistically significant. All statistical calculations will be performed using SPSS10.0 (SPSS, Chicago, IL, USA).

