## Background

To date, pancreaticoduodenectomy (PD) has been regarded as the only potentially curative treatment for pancreatic head and periampullary tumors, including tumors in the ampullary region, distal biliary duct, and periampullary duodenum [1]. A retrospective study in which 1000 cases were recruited over the past three decades showed that PD has become an effective treatment to reduce hospital mortality [2]. Mortality has been reduced to less than 5 %, but the morbidity remains at 30–50 % [2, 3]. Postoperative pancreatic fistula (POPF) is one of the most frequent and ominous complications after PD, and its occurrence reportedly ranges from 2–40 % [4, 5]. Severe POPF prolongs hospital stay and requires the use of specific treatments, such as the use of antibiotics, nutritional support, endoscopy, interventional radiology, and/or reoperation, etc. [6]. POPF risk is increased by many factors including pancreatic texture, main pancreatic duct diameter, and pancreaticojejunal (PJ) anastomotic technique [7–9]. Among these factors, only anastomotic technique can be improved. According to the International Study Group of Pancreatic Surgery (ISGPS) definition, POPF exists if the drainage of any measurable volume of fluid containing amylase exceeds three times the normal serum value on or after postoperative day (POD) 3 [10].

Several anastomotic surgical techniques have been developed to reduce the incidence of pancreatic fistula in recent decades, including the duct-to-mucosa method, pancreaticogastrostomy, Peng’s binding method, and the “end-to-end” or “end-to-side” invaginated method. Among these techniques, the conventional duct-to-mucosa method remains the most popular anastomosis due to its advantages. The size of the pancreatic remnant is not limited; moreover, the jejunal lumen and pancreatic remnant lead to easier anastomosis [11–14].

Compared with two-layer duct-to-mucosa anastomosis, the novel one-layer duct-to-mucosa PJ anastomosis method has been reported to be efficient at reducing POPF occurrence [15, 16]. However, the two cited retrospective studies might lead to selection bias. Because this evidence is insufficient, we will conduct a randomized controlled trial to verify the superiority of one-layer duct-to-mucosa PJ anastomosis after PD over the two-layer technique.

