#### Secondary endpoints

Secondary outcomes will be postoperative hospital stay, anastomosis time, postpancreatectomy hemorrhage, biliary leak, delayed gastric emptying, wound infection, intra-abdominal fluid collection or abscess, relaparotomy, and mortality. Existent ISGPS definitions will be used to ensure the comparability and generalizability of the results (Table 1). Postoperative complications will be graded based on severity according to the Clavien-Dindo definition [18] (Table 2).

**Table 1 Tab1:** Definition of secondary endpoints

Secondary endpoint	Definition and assessment of outcomes
Anastomosis time	Time from beginning to end of PJ anastomosis
Mortality	Death due to any cause until 90 days after the operation and the reason
Morbidity	Postoperative complications will be recorded until 90 days after operation. The severity of complications will be graded according to the Clavien-Dindo classification [18]
Postoperative hospital stay	Time from day of operation until discharge (days)
Postpancreatectomy hemorrhage	Evidence of blood loss from drains and/or nasogastric tube, based on ultrasonography, as defined by ISGPS [19]
Biliary leak	Bilirubin concentration in the drain fluid at least three times the serum bilirubin concentration as defined by International Study Group of Liver Surgery [20]
Delayed gastric emptying	Failure to resume solid diet with prolonged need for nasogastric tube as defined by ISGPS [21]
Intra-abdominal fluid collection	Collection of fluid measuring ≥3 cm associated with clinical or laboratory abnormalities
Wound infection	Surgical site infection associated with laparotomy that develops during the initial hospital stay
Pneumonia	Presence of a new infiltrate on chest X-ray, as well as following: body temperature >38 °C, abnormal elevation of white blood cells, or positive sputum, and requiring antibiotic treatment
Abdominal rupture	Dehiscence of abnormal closure with need for resuture of the laparotomy during the initial hospital stay

**Table 2 Tab2:** Complication grades according to the Clavien-Dindo classication scheme^a^

Grade	Definition
I	Any deviation from the normal postoperative course without the need for pharmacological treatment or surgical, endoscopic, and radiological intervention
II	Requiring pharmacological treatment with drugs other than those allowed for grade I complications
III	Requiring surgical, endoscopic, or radiological intervention
IIIa	Intervention not under general anesthesia

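### Anastomosis time depends on the operator but gets an unadjusted two-sample test; if several surgeons operate, a surgeon term would buy precision cheaply

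*Protocol article*

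**What the plan says.** All references are to the protocol article.

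- **Endpoint.** Anastomosis time is a listed secondary endpoint and is also named in the Study aim. Table 1 defines it as "Time from beginning to end of PJ anastomosis".
- **Test.** Under Statistical analysis, background characteristics and surgical outcome measures that are continuous are compared by "two-tailed *t* tests or nonparametric Mann–Whitney *U* tests for continuous variables". The sentence does not name anastomosis time, but as a continuous surgical outcome it belongs there, and no other method is given for it.
- **Covariates.** The primary test adjusts for pancreatic texture and main duct diameter. The section then adds: "A binary logistic regression will be applied to compare the POPF occurrence rates between the groups after adjusting for other factors". Those other factors are not listed.
- **Allocation.** Under Randomization, numbers are computer-generated at 1:1 and no stratification is described. On timing: "The envelopes will be opened before PJ reconstruction and after resection of the lesion from the pancreatic or periampullary region".
- **Operators.** The number of surgeons is not stated. The plural appears under Blinding: "Blinding of the surgeons and people involved in the operation is not feasible due to the nature of the interventions".

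**The concern.** How long an anastomosis takes depends on who performs it as well as on the technique. If several surgeons operate and the analysis ignores which one did, differences between them go into the residual variation. The interval for the difference in anastomosis time between techniques is then wider than it need be. The primary model already adjusts for two patient features, but operator, an obvious predictor of this secondary endpoint, is not used for it.

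A second, smaller point concerns timing. The envelope is opened during the operation in front of a team that cannot be blinded. Unless the operator is settled and recorded beforehand, the trial record cannot show that the choice of operator was independent of the arm drawn. Randomization protects whatever was fixed before the envelope was opened, not a decision made afterwards.

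**Working it through.** **1. The plan's own figure.** The sample size rests on POPF alone: 4.5% against 26.7%, 90% power, two-sided 5%. With the unpooled two-proportion formula:

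n = (1.960 + 1.282)² × [0.045 × 0.955 + 0.267 × 0.733] / 0.222²
= 10.51 × 0.2387 / 0.04928 = 50.9, so 51 per group.

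102 / 0.9 = 113.3, so 114 in total. Both figures reproduce, and neither depends on anastomosis time or operator.

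**2. Is the unadjusted test valid?** Each patient is randomized individually, so a surgeon's general speed or skill is spread over both arms by chance and does not shift the expected difference. This was checked by simulation under assumed conditions: 4 surgeons, 102 patients, no true difference, 6,000 runs per setting. The type I error of the unadjusted t test was 4.5%, 5.5% and 4.9% at a surgeon variance share of 0.05, 0.20 and 0.40. The nominal 5% is held to within simulation error (sqrt(0.05 × 0.95 / 6000) is about 0.3 points).

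**3. What precision is lost?** Let rho be the share of the within-arm variance in anastomosis time that lies between surgeons. The documents give no value, so a range is assumed. Adjustment leaves a residual variance of (1 − rho) times the unadjusted one. Hence:

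- standard error, unadjusted over adjusted = 1/sqrt(1 − rho)
- patients needed by the unadjusted test for the same precision = 1/(1 − rho) times as many
- patients whose information is lost, out of 102 = 102 × rho

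| assumed rho | SE ratio | extra patients needed | lost out of 102 |
|---|---|---|---|
| 0.05 | 1.03 | 5% | 5 |
| 0.10 | 1.05 | 11% | 10 |
| 0.20 | 1.12 | 25% | 20 |

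The last two columns express the same loss. For example, at rho = 0.20, 102 − 20.4 = 81.6 adjusted patients are worth 102 unadjusted ones, and 102 / 81.6 = 1.25.

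**4. The same in power.** In the simulation with an assumed true difference of 0.55 SD, adding surgeon to the model raised power from 79% to 80% at rho = 0.05 and from 81% to 86% at rho = 0.20. At a high rho of 0.40 it went from 82% to 94%. With 4 surgeons the residual degrees of freedom fall from 102 − 2 = 100 to 102 − 5 = 97, which is negligible.

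**5. Does the same device suit POPF?** At the planned rate the one-layer arm expects 51 × 0.045 = 2.3 events. Split by surgeon, most strata would have no event in that arm, so a POPF comparison stratified by surgeon would be too sparse to help.

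**The case against.** The strongest reply is that nothing here is an error. A two-sample test under individual randomization is correct, and step 2 confirms it. The number of operators is unknown. The trial has one center, and the plural in the blinding sentence may be no more than a general phrase; with a single operator the loss is zero. The unlisted other factors in the logistic model might include operator, although that model concerns POPF and not anastomosis time. Operator credentials and staffing rules may sit in the full protocol, which is not shown. All of this stands, and it makes the point conditional and small. It does not remove it, because the unadjusted test for continuous surgical outcomes is stated in the article itself.

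Three stronger readings are tempting, and the documents do not support them.

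- **Surgeon differences bias the comparison.** They do not under individual randomization; they add noise. Bias would need skill that differs by technique, or a change of operator made because of the arm drawn. Nothing in the article says that either occurs.
- **A learning curve handicaps the one-layer arm.** The Background says that "the novel one-layer duct-to-mucosa PJ anastomosis method has been reported to be efficient at reducing POPF occurrence". This places the method in the literature. It does not say that this team lacked experience with it. A surgeon term would not remove a learning effect in any case.
- **The POPF result is at risk by a definite amount.** One event in 51 moves an arm by 2.0 points whatever its cause. That is not an estimate of a surgeon effect.

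**Conclusion.** This is a cheap improvement, not a defect. The planned analysis of anastomosis time is valid. If more than one surgeon performs the anastomosis, it gives up precision worth about 11% more patients at an assumed surgeon variance share of 10%, and about 25% at 20%. The size rests wholly on that assumed share and on there being several operators; the article gives neither. The point concerns one secondary endpoint. The primary POPF test, the 51 per group and 114 in total, and the type I error are unchanged. Recording the operator before allocation is a safeguard against a possibility that the article leaves open, not a response to anything it reports.

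**What to change.** 1. **Randomization and CRF.** Before the envelope is opened, record on the CRF the surgeon who will do the anastomosis whichever arm is drawn. Document any later change of operator with its reason, and keep the patient in the randomized arm for analysis.
2. **Statistical analysis.** If there is more than one operator, compare anastomosis time by a linear model with arm and surgeon, on the log scale if the times are skewed, in place of the unadjusted test. Use the surgeon recorded before allocation, so that the covariate cannot depend on the arm. With a single operator, say so and keep the present test.

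Do not add a surgeon-stratified POPF analysis; about 2 expected one-layer events cannot support it.

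The cost is one CRF entry (plus a note of any change), a sentence in each of the two sections, a few degrees of freedom and slightly less flexibility in staffing after allocation. No extra patients are needed.

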### Patient involvement

Sample size calculation is based on the primary endpoint: POPF rate. According to published data, an assumed absolute risk of 22 % difference in POPF occurrence is the appropriate basis for the calculation assuming 4.5 % POPF in the one-layer technique group and 26.7 % in the two-layer technique group [15, 16]. This calculation yields a total of 51 patients in each group, which assures a power of 90 % at a two-sided level of significance of 5 % (NCSS and PASS 11 (NCSS Statistical Software, Kaysville, UT, USA)). Assuming an expected withdrawal rate of 10 % during the trial, 12 additional patients will be included and randomized; therefore, the total sample size required is *n* = 114 patients (Fig. 1) (Additional files 1 and 2).

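### Secondary outcomes are compared without the two prognostic covariates already chosen for the fistula analysis, which gives up precision (minor)

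*Protocol article*

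**What the plan says.** In the Protocol article, Statistical analysis, the fistula hypothesis is tested with adjustment for texture (soft or hard) and duct diameter (cut at 3 mm). A logistic regression for POPF with other factors is added. For the rest, "Background characteristics and surgical outcome measures will be compared using chi-squared" or Fisher's test if categorical, and with t or Mann-Whitney tests if continuous. No covariate is named for these comparisons. The threshold is P < 0.05.

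On balance between the groups, the section says "The homogeneity of two groups will be described by comparison of the demographic data and baseline values". It gives no criterion for homogeneity and makes no analysis depend on it.

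Three other places bear on the point:

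- Background: "POPF risk is increased by many factors including pancreatic texture, main pancreatic duct diameter" (anastomotic technique is the third factor named). The same section says that severe fistula prolongs hospital stay.
- Randomization: "computer-generated random numbers with an allocation ratio of 1:1 (an equal probability of assignment to either group"). No stratification is described. The envelope is opened after resection and before the pancreaticojejunal reconstruction.
- Secondary endpoints: postoperative stay is one of the listed outcomes.

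**The concern.** The plan treats texture and duct diameter as important enough to adjust the primary endpoint. It then leaves them out of the secondary comparisons, including hospital stay, which its own Background links to severe fistula. Because the two factors are not described as stratification factors, only chance balances them between groups of about 57. An unadjusted test leaves the variation they explain in the error term. It also cannot correct for whatever imbalance this one randomisation happens to produce.

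What is at stake is the precision of the secondary results and how well they can be interpreted if the groups turn out uneven. The validity of the trial is not at stake.

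The baseline tests do not help here. Under proper randomisation the baseline null hypothesis is true by design, so a P value cannot show whether an observed imbalance matters for an outcome, and a non-significant one does not establish that the groups are alike.

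**Working it through.** **1. The plan's own sample size (Patient involvement).** Inputs: "assuming 4.5 % POPF in the one-layer technique group and 26.7 % in the two-layer technique group", 90% power, two-sided 5%. With the unpooled formula:

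n = (1.960 + 1.282)² × [0.045 × 0.955 + 0.267 × 0.733] / 0.222² = 10.507 × 0.2387 / 0.04928 = 50.9, so 51 per group.

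This matches the stated figure. With 10% withdrawal, 102 / 0.90 = 113.3, so 114 in total or 57 per group, also as stated. The check below uses 57 per group.

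**2. Precision lost without adjustment.** For a 0.5-SD difference the noncentrality is 0.5 × √(57/2) = 2.669. If the covariates explain a share R² of the outcome variance, it becomes 2.669 / √(1 − R²). The documents do not give R², so a range is assumed.

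| R² (assumed) | Noncentrality | Power, two-sided 5% | Equivalent unadjusted n per group, 57/(1 − R²) |
|---|---|---|---|
| 0 (unadjusted) | 2.669 | 75% | 57 |
| 0.09 | 2.798 | 79% | 63 |
| 0.16 | 2.912 | 82% | 68 |
| 0.25 | 3.082 | 86% | 76 |

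This gain does not depend on an imbalance occurring.

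**3. Validity over all randomisations.** A simulation of 400,000 trials at 57 per group had no treatment effect, 50% soft glands, and a binary secondary outcome with risk 20-40% in soft and 10% in hard glands (all assumed). The unadjusted chi-squared test had type I error 5.1-5.2% and a mean group difference of 0. The unadjusted tests are therefore sound on average.

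**4. Exposure in the particular trial.** At an assumed 50% prevalence of soft glands, exact binomial enumeration gives a texture imbalance of at least 10 percentage points in about 30% of trials. A gap of at least 9 patients (9/57 = 15.8 points) arises in about 11%. In about 25% of trials the imbalance is at least 10 points and still not significant by chi-squared.

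- *Binary outcome, risks as in step 3.* The shift in the risk difference is (risk in soft − risk in hard) × imbalance. For imbalances of 10 to 18 points it runs from 0.10 × 0.10 = 1.0 point to 0.30 × 0.18 = 5.4 points, against a standard error of 6.7-8.1 points. Given a non-significant imbalance of at least 10 points, type I error is 5.2-6.3%. Given one of at least 15 points, it is 5.5-7.8%.
- *Continuous outcome, fixed split of 28 against 37 soft glands (chi-squared P = 0.089).* The standardised imbalance is 0.158 / √(0.570 × 0.430) = 0.32. With an assumed texture-outcome correlation of 0.3 to 0.5 the shift is 0.10 to 0.16 SD, against a standard error of √(2/57) = 0.19 SD. Type I error given that split is about 7-10% unadjusted and about 5% adjusted.

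**The case against.** The strongest reply is that unadjusted comparison of secondary outcomes in a randomised trial is legitimate, that the primary endpoint is already protected by a pre-specified adjustment, and that modelling details may sit in an analysis plan that is not shown. The first two points stand, and they are why this is minor. The third is weaker: the article does not leave the method open but names unadjusted tests for these outcomes.

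A reader might infer that homogeneity is to be judged by P ≥ 0.05, so that imbalance passes unchecked into the results. The text does not support this. Homogeneity is only described, alongside frequencies, percentages, means and standard deviations by group. Nothing is gated on it, and texture and duct diameter are not stated to be among the baseline values compared.

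A reader might also take the 7-10% error rate as the error rate of the planned tests. It holds only for a chosen, fairly extreme split and an assumed correlation. In every scenario tried the shift is below one standard error.

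It is tempting, too, to quote how often a baseline test misses a true difference of a given size. Under randomisation there is no true baseline difference to miss, so those rates carry no weight.

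It is fair to add that the documents tie the two factors to fistula, and severe fistula to hospital stay, but not to anastomosis time, hemorrhage or delayed gastric emptying. For those outcomes the gain may be small.

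**Conclusion.** The point holds as a matter of efficiency and is minor. The unadjusted secondary tests are valid, with about 5% type I error over all randomisations. They forgo precision that data already required for the fistula analysis could supply: power for a 0.5-SD effect would rise from 75% to 79-86% if the covariates explain 9-25% of the variance. That share is an assumption, as are the soft-gland prevalence and the correlations used above. The case is best documented for postoperative stay. Testing the baseline table is a reporting weakness only. Neither matter changes the sample size of 114, the fistula analysis or any stated decision.

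**What to change.** In the Statistical analysis section, pre-specify that postoperative stay (suitably transformed) and the other secondary outcomes with enough events are compared with adjustment for texture and main duct diameter, in the categories already set for POPF. State that both are assessed before the envelope is opened, so that knowledge of the allocation cannot influence them. Keep Fisher's exact test for rare outcomes such as mortality and relaparotomy.

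For the baseline table, take background characteristics out of the list of tested variables, summarise them by group without P values, and draw no conclusion of homogeneity from non-significance.

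The cost is a few extra models and some rewording. No further patients or procedures are needed. The Trial status section says that recruitment was under way, so the change is best made before outcomes are seen. Covariates added after an imbalance is noticed would be data-driven.
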